#### Pelvic pressure assessment

To assess the strength of the pelvic floor muscles, we used a biofeedback device that measures pressure in millimeters of mercury (mmHg) through an inflated vaginal probe. This information was displayed analogically on a manometer. The evaluation took place with the participant in a gynecological position, exposing areas of the abdomen, pelvic floor, and legs, enabling a more precise analysis of pelvic muscle contraction [36].

To insert the vaginal probe of the dynamometer, an unlubricated male condom was used to cover it, as sterilization is not feasible. A water-based lubricating gel was applied to the external part of the male condom to ease insertion for women with insufficient vaginal lubrication. The pressure sensor was inserted into the vaginal canal and resting vaginal pressure (muscle relaxation) was measured. The device was calibrated and adjusted, and the participant was instructed to contract her pelvic floor muscles as strongly as possible three times, maintaining the contraction for at least five seconds (maximum vaginal pressure), with a 30-second interval between each contraction. The minimum vaginal pressure was measured during relaxation of the contractions [37].

#### Urinary loss assessment

The Pad Test, also known as the 1-hour pad test, is an effective method for assessing urinary leakage and categorizing Stress Urinary Incontinence (SUI) into mild, moderate, and severe levels. This method is validated by the Standardization Committee of the International Continence Society (ICS) and allows for the measurement of lost urine by weighing the absorbent pad [11].

To perform the Pad Test, the participant should place a pre-weighed absorbent pad near the external urethral opening and drink 500 mL of water, remaining at rest for 15 minutes. Then, she performs activities simulating daily actions such as walking, sitting and standing up ten times, coughing ten times, picking up objects from the floor five times, jogging in place for a minute, and washing hands under running water for a minute. After completing these activities, the absorbent pad is removed and weighed on a precision scale with a minimum reading of 0.1 mg and a maximum capacity of 220 g. Urinary losses are classified as insignificant (up to 1 g), mild (from 1.1 to 9.9 g), moderate (from 10 to 49.9 g), and severe (above 50 g) [38].

### Statistical analysis

The data will be tested for normality using the Shapiro-Wilk test, and those with parametric distribution will be represented by their respective means and standard deviations. In cases where the assumption of parametric distribution is rejected, medians and quartiles will be used. To assess the association between the studied groups and the independent variables, Student’s t-test or Wilcoxon-Mann-Whitney test will be used for parametric and non-parametric data, respectively. All tests will be two-tailed, and the adopted significance level is α = 0.05. The results will be organized in excel spreadsheet and the inferential analysis will be conducted using R.

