**Method:**

In this randomized, double-blind, placebo-controlled study protocol, women over 50 years of age who are in the postmenopausal period (amenorrhea for at least 12 months, with no pathology involved) with one or more symptoms of GSM will be randomly divided into two groups. The treatment group (n = 30) will receive four consecutive applications, weekly, using DMC laser diode (λ = 808 nm), 4J per point, 100mW of power, 1,016W/cm^2^, 8 sites in the vulvar region, The Placebo Group (n = 30) will be handled as treated, but with the laser turned off. The quality of life will be assessed using female sexual functioning index (FSFI-6), urinary incontinence questionnaire (ICIQ-SF), Quality of life will be analyzed using the female sexual functioning index (FSFI-6). The intensity of menopausal symptoms will be evaluated using a visual analogue scale (VAS), the vulvo vaginal atrophy will be measured by the Vaginal Health Index (VHI). Also, the vaginal temperature will be measured using a thermal camera, the pressure of the pelvic floor force (vaginal dynamometer) and a 1-hour Pad Test will be performed to quantify the urinary loss. With this procedure, we intend to obtain an overall better life quality and diminished symptoms in women with GSM. All assessments will be performed prior to the first irradiation and after the last one.

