### Sample size and participants

Since the literature lacks studies on the effects of the photobiomodulaton on GSM, the sample size was calculated using the formula described using the estimated effect size, as described by Kadam and Bhalerao [29]. Considering a type I error of 0.05 and a test power of 80%, the calculated sample size was 60 participants, with 30 in each group (A and B). The Fig 3 shows that, for medium (0.750) and large effects (1.000–1.250), a minimum of 30 patients per group is sufficient to control statistical variance, ensuring a test power greater than 0.80. Considering a 10% of sample loss, a total of 66 patients will be recruited for the study. The Fig 3 shows a plot of the test power as a function of the sample size and estimated effect size.

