### Randomization

The participants were randomly assigned to two groups, Group A (treatment) and Group B (placebo), in block-randomization fashion, with each block comprising four participants. After participant selection and assessment, sealed brown envelopes were randomly assigned to each subject containing the treatment allocation until the block was over, afterwards a new block of four allocation (two in each group) was made.

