#### Vulvar temperature

The vulvar temperature measured in degrees Celsius, will be evaluated at the same eight points that were irradiated in the vulvar region using a digital infrared thermometer, allowing for non-contact measurements. The average of the eight readings will be calculated before and after each of the four consecutive weekly sessions of diode laser treatment.

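### Vulvar temperature is recorded eight times per woman, but only tests for independent groups are named and the temperature value to be compared is not fixed

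*Protocol article*

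**What the plan says.** - **Unit of randomisation.** The Randomization section allocates individual women: "The participants were randomly assigned to two groups, Group A (treatment) and Group B (placebo), in block-randomization fashion".
- **Temperature readings.** Under Vulvar temperature, the outcome "will be evaluated at the same eight points that were irradiated in the vulvar region using a digital infrared thermometer". The sites are averaged, and the average is repeated over time: "The average of the eight readings will be calculated before and after each of the four consecutive weekly sessions of diode laser treatment". No averaging over sessions is described.
- **Conflicting schedule.** The Abstract's Method paragraph states: "All assessments will be performed prior to the first irradiation and after the last one". That would leave two temperature means per woman instead of eight.
- **Tests.** The Statistical analysis section introduces its tests with "To assess the association between the studied groups and the independent variables" and then says that "Student’s t-test or Wilcoxon-Mann-Whitney test will be used for parametric and non-parametric data, respectively". It adds: "All tests will be two-tailed, and the adopted significance level is α = 0.05". Temperature is not treated as an exception. No time point, change score, per-woman summary or repeated-measures method is named for it.

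**The concern.** Both named tests assume that the observations within each arm are independent. They suit an outcome with one analysed value per woman. Under the Methods schedule, temperature has eight, and the readings of one woman will resemble each other. The section gives one rule for all data and does not reduce temperature to a single value, so several analyses are compatible with the text:

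- test the arms at each time point, which gives up to eight tests of one outcome at 0.05, one of them on readings that the laser cannot have influenced;
- test one chosen time point or change score, which is valid but leaves the choice to the analyst;
- test one summary per woman, which is valid and can use all the readings.

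The first raises the false-positive rate for the outcome as a whole. Because the text does not choose, the choice could also be made after the results are seen. Either way, a reported temperature difference would be harder to interpret than it need be.

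**Working it through.** **Inputs from the article.** There are 30 women per arm, two-sided alpha 0.05 and 80% power, and the smallest standardised effect listed is 0.75 (Sample size and participants). There are m = 2 × 4 = 8 temperature means per woman (Vulvar temperature).

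**Assumed input.** The within-woman correlation ρ between temperature means is not given. It is taken as equal for all pairs of readings, with ρ = 0.3, 0.5 and 0.7.

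**1. The plan's own figure.** For a two-group comparison with one value per woman, n per arm = 2(1.96 + 0.84)² / 0.75² ≈ 27.9, so 28; the exact t-test needs 29. With 30 per arm the t-test has power 0.815 at 0.75 SD. The stated power above 0.80 is reproduced, with one value per woman.

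**2. Eight separate tests at 0.05.** If the readings were independent, the chance of at least one false positive would be 1 − 0.95⁸ = 0.34. Correlation lowers it. Simulation with no effect (normal readings, 6,000 to 20,000 trials per setting, several runs) gives:

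| ρ | At least one of eight tests significant |
|---|---|
| 0.3 | 0.30 to 0.31 |
| 0.5 | 0.25 |
| 0.7 | 0.19 to 0.21 |

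**3. Pooling all eight readings as independent** (not stated in the text; shown for scale only). The variance of the arm difference is understated by the factor 1 + (m − 1)ρ, so the true error rate is 2[1 − Φ(1.96 / √(1 + 7ρ))]:

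| ρ | 1 + 7ρ | Error rate |
|---|---|---|
| 0.3 | 3.1 | 0.27 |
| 0.5 | 4.5 | 0.36 |
| 0.7 | 5.9 | 0.42 |

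Simulation agrees (0.26 to 0.27, 0.36, 0.42 to 0.44), and the Wilcoxon-Mann-Whitney test behaves similarly.

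**4. One value per woman.** A t-test on each woman's mean has a simulated error rate of 0.047 to 0.054, and a test on one time point is also at about 0.05.

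**5. Which single contrast?** Suppose, unfavourably for averaging, that the effect builds up linearly to 0.75 SD after session 4. The effects on the seven readings after baseline are then 1/4, 1/4, 1/2, 1/2, 3/4, 3/4 and 1 times 0.75, with mean 0.75 × 4/7 = 0.429. Power uses a two-sample t-test with 30 per arm. Adjustment for the reading before session 1 subtracts ρ² from the variance:

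- last reading, unadjusted: variance 1, power 0.81;
- last reading, adjusted: variance 1 − ρ²;
- mean of seven later readings, adjusted: variance (1 + 6ρ)/7 − ρ²;
- mean of the three pre-session readings at sessions 2 to 4, unadjusted: effect 0.75 × 1/2 = 0.375, variance (1 + 2ρ)/3.

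| ρ | Last, adjusted | Mean of seven, adjusted | Mean of three pre-session, unadjusted |
|---|---|---|---|
| 0.3 | 0.85 | 0.83 | 0.50 |
| 0.5 | 0.91 | 0.82 | 0.42 |
| 0.7 | 0.98 | 0.90 | 0.36 |

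Both adjusted contrasts exceed 0.80 in this setting. If instead the effect is constant from the first session, averaging is favoured: at ρ = 0.5 and 0.75 SD, even the unadjusted mean of three pre-session readings has power 0.94, against 0.81 for the last reading alone.

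**The case against.** The strongest reply is that the named tests are not wrong. Applied to one summary per woman they hold 0.05, and which summary is tested is a detail that a condensed article may leave to an analysis plan that is not shown. Comparing only the final reading is also valid. It fits the Abstract's schedule, and its power of 0.81 at 0.75 SD meets the plan's own target. With several time points tested, each single test still keeps its 0.05; only the overall rate rises.

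Much of this stands. A reader might infer that the plan will treat repeated readings as different women, or that any use of the named tests must either inflate the error rate or waste most of the data. The documents support neither. Nothing says that session values will be pooled; the eight sites are averaged, and the sample size counts women. The per-woman summary is a valid route that avoids both faults.

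What does not fall away is that the Statistical analysis section is not silent: it fixes the tests and the level for all data, while the Methods fix an outcome repeated eight times. Read literally at each time point, the two together give the rates in step 2, and nothing in the text excludes that reading. A woman-level analysis with baseline adjustment is better at almost no cost.

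**Conclusion.** The point holds as a minor one. Temperature yields eight correlated means per woman under the Methods, only independent-group tests at 0.05 are named, and the value to be compared is not fixed. Separate tests at every time point would carry about a 0.20 to 0.31 chance of at least one false positive; pooling, which is not stated, would carry 0.27 to 0.42; one value per woman carries 0.05. Inflation is therefore a risk that the text leaves open, not something that it prescribes.

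The sizes rest on an assumed equal correlation of 0.3 to 0.7 and normal readings. The count of eight rests on the Methods schedule; the Abstract's schedule would give two. The weight is limited because temperature is one of several outcomes, does not appear in the stated objective or hypothesis, and does not drive the sample size.

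**What to change.** In the Statistical analysis section, state that vulvar temperature is analysed with the woman as the unit, by either:

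- a linear mixed model with a random intercept per woman and the reading before session 1 as covariate; or
- ANCOVA on one summary per woman with the same covariate.

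Make no arm test on the reading before session 1. Name one arm contrast in advance, for example the mean of all seven later readings or the reading after session 4. Show session-specific estimates and within-session changes descriptively. Reconcile the Abstract with the Vulvar temperature section on when temperature is measured.

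The cost is a sentence or two and a few lines in R, which the plan already uses; no further data or participants are needed. The small downside is that any single contrast is less sensitive to some patterns: an average loses power if the effect builds up late, and a last-reading contrast uses less of the data.

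### Free gain in efficiency: adjust each outcome for its own baseline instead of using an unadjusted two-sample test, and fix the effect measure in advance instead of letting Shapiro-Wilk choose it

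*Protocol article*

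**What the plan says.** The Statistical analysis section first sets a gate: "The data will be tested for normality using the Shapiro-Wilk test". The result decides how data are summarised and which two-sample test compares the groups: Student's "t-test or Wilcoxon-Mann-Whitney test will be used for parametric and non-parametric data, respectively". The section adds that "All tests will be two-tailed, and the adopted significance level is α = 0.05". It names no covariate, regression model or change score, and does not say whether post-treatment values or changes enter the test.

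Baseline values will exist. The abstract's Method paragraph says: "All assessments will be performed prior to the first irradiation and after the last one". The Research flow section places the first pelvic pressure and urinary loss measurements before random assignment.

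The Sample size section states: "Considering a type I error of 0.05 and a test power of 80%, the calculated sample size was 60 participants". It adds that "for medium (0.750) and large effects (1.000–1.250), a minimum of 30 patients per group is sufficient". The Randomization section gives 1:1 allocation: "a new block of four allocation (two in each group) was made".

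**The concern.** A baseline is collected, but the comparison gives it no stated role. If post-treatment values are tested, the part of the between-woman variation that baseline could explain stays in the error term. If change scores are tested, baseline is used, but with a fixed slope of 1 rather than the slope the data support, which is less efficient.

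This matters because the trial is small and its planning effect is a guess. The Sample size section itself says that the literature lacks studies of this treatment in the condition. If the true effect is smaller than 0.75 standard deviations (SD), unadjusted power falls quickly, and precision already paid for by the baseline visit is worth having.

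A second, milder point concerns the gate. A t-test compares means, whereas a Mann-Whitney test compares rank distributions. When a normality test on the trial's own data picks between them, outcome by outcome, no outcome has an effect measure fixed in advance.

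**Working it through.** **Inputs from the article.** 30 per arm and standardised effects of 0.75 to 1.25 (Sample size section); 1:1 allocation (Randomization section); two-sided α = 0.05 (Statistical analysis section).

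**Assumed input.** The correlation r between an outcome's baseline and post-treatment value is not given. I show r = 0.1 to 0.7.

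**Step 1: reproduce the plan's figure.** For a two-sample t-test with n per arm, the noncentrality is d × √(n/2) on 2n − 2 degrees of freedom. With n = 30 and d = 0.75 this is 0.75 × √15 = 2.905 on 58 degrees of freedom, with critical value 2.002. Power is 0.815. For d = 1.00 and 1.25 it is 0.968 and 0.997. The claim of power above 0.80 with 30 per group is reproduced. The difference detectable with 80% power is 0.736 SD.

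**Step 2: three ways to use the data.** Relative to a test on post-treatment values (variance factor 1):

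- ANCOVA has variance factor 1 − r², so the effective d is 0.75/√(1 − r²), on 57 degrees of freedom.
- Change scores have variance factor 2(1 − r), so the effective d is 0.75/√(2(1 − r)), on 58 degrees of freedom.

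At r = 0.5, for example, ANCOVA has effective d = 0.75/√0.75 = 0.866. The change score has 0.75/√1 = 0.75, the same as the post-treatment value alone.

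| r (assumed) | Post-treatment value, unadjusted | Change score | ANCOVA | Detectable at 80% power, ANCOVA |
|---|---|---|---|---|
| 0.1 | 0.815 | 0.567 | 0.819 | 0.732 SD |
| 0.3 | 0.815 | 0.675 | 0.849 | 0.702 SD |
| 0.5 | 0.815 | 0.815 | 0.909 | 0.637 SD |
| 0.7 | 0.815 | 0.958 | 0.979 | 0.525 SD |

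The formula charges ANCOVA one degree of freedom but not the small further cost of estimating the slope. The 0.1 row should therefore be read as no practical gain over the unadjusted test.

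**Step 3: a smaller effect.** At d = 0.5, unadjusted power on post-treatment values is 0.478. ANCOVA gives 0.514, 0.594 and 0.760 at r = 0.3, 0.5 and 0.7.

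**Step 4: in patients.** At r = 0.5, 30 × (1 − 0.25) = 22.5 women per arm under ANCOVA carry about the information of 30 per arm unadjusted.

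**Step 5: the Shapiro-Wilk gate.** The two-stage rule was simulated at 30 per arm, applying the t-test if both arms passed and Mann-Whitney otherwise. Type I error was 0.051 (normal), 0.044 (log-normal) and 0.053 (gamma). Under normal data with d = 0.75, its power was 0.810 against 0.812 for the t-test. Under the skewed distributions it had more power than the t-test. The gate costs essentially nothing in power or error control.

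**The case against.** The strongest reply is that nothing here is wrong, only less efficient than it could be. In a randomised trial the unadjusted comparison is unbiased, its significance level already allows for chance baseline imbalance, and the trial meets its own power target. All of this stands. A reader might infer that the trial is underpowered or that baseline imbalance invalidates the result; neither follows.

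Several other stronger readings also fail:

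- *The baseline is wasted.* This would be so only if post-treatment values are compared, and the article does not say. Under change scores the baseline is used, and at r = 0.7 the shortfall against ANCOVA is small (0.958 against 0.979). At low correlations it is large (0.675 against 0.849 at r = 0.3).
- *The pre-test loses power or inflates error.* Step 5 shows otherwise. Only the unfixed effect measure remains.
- *Pad weight will almost certainly fail Shapiro-Wilk, with a large loss.* The Urinary loss assessment section gives severity classes ("Urinary losses are classified as insignificant (up to 1 g), mild (from 1.1 to 9.9 g" and upwards), not the distribution expected here, and the inclusion criteria set no pad-weight threshold. Simulated gains for a log-transformed ANCOVA rest on an assumed log-normal distribution that favours it.

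The size of the gain also depends on an unknown correlation and may be close to nil if that is low. This too stands.

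One reply does not hold: that the matter is simply left to a fuller plan. The article names its method, so a later plan using ANCOVA would change stated text rather than fill a gap.

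**Conclusion.** The point holds as a free improvement in efficiency, graded should-fix. The planned analysis is valid and reaches 0.815 power at d = 0.75. For the same women and visits, ANCOVA would give about 0.82 to 0.98 as r runs from 0.1 to 0.7. It is above a change-score test at every correlation shown, whichever quantity the authors had in mind. The figures rest on the assumed correlations, a linear relation with baseline, equal variances, and 30 analysed women per arm.

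The Shapiro-Wilk rule is a separate and lesser fault: it leaves the choice between a difference in means and a comparison of ranks to the trial data.

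**What to change.** In the Statistical analysis section:

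1. State that each outcome measured before the first and after the last session is compared by linear regression of the post-treatment value on treatment group and that outcome's baseline value, reporting the adjusted difference with its 95% confidence interval.
2. For skewed outcomes such as pad weight, choose one version now: ANCOVA on log(1 + grams) or a rank-based ANCOVA. Neither gives a difference in grams, so state how the result will be expressed.
3. Remove Shapiro-Wilk as the rule for choosing the test. It may stay as a description of the data.
4. For vulvar temperature, which is averaged over eight points before and after each of four sessions, first name the reading to be analysed. One option is the reading after the last session, adjusted for the reading before the first.

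The cost is wording only: no further patients, visits or measurements. The sample size can stay as it is, since the present calculation becomes conservative to the extent that baseline predicts outcome.

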### Outcomes

#### Questionnaires

A questionnaire will be administered to the participants during their initial outpatient consultation conducted by the researcher to gather sociodemographic information.

To assess quality of life and sexual satisfaction, validated questionnaires in Brazil will be employed. The Female Sexual Function Index (FSFI) is a tool used to evaluate female sexual response across six domains: desire, arousal, lubrication, orgasm, satisfaction, and pain [30, 31].

The International Consultation on Incontinence Questionnaire—Short Form (ICIQ-SF) is a questionnaire designed to assess the impact of Urinary Incontinence (UI) on quality of life and quantify urinary loss in both male and female patients [32].

The methods for evaluating Genitourinary Syndrome of Menopause (GSM), which describe the participants’ perception of clinical symptoms before and after the proposed treatment, include the Vaginal Health Index Score (VHI). This method encompasses a clinical assessment during a speculum examination, covering five parameters: elasticity, pH, mucosal appearance, moisture, and the presence of vaginal secretion. A qualified healthcare professional will conduct this evaluation during the physical examination, allowing for the diagnosis of Vulvovaginal Atrophy (VVA) [33].

Vaginal pH evaluation will be performed using a pH indicator strip inserted into the middle third of the vagina, in contact with the mucosa, causing a color change in the strip. The nitrazine strip should remain in contact with the vaginal wall for 5 seconds before checking the pH on the colorimetric scale provided by the manufacturer [34].

The Visual Analog Scale (VAS) will be applied as an instrument for assessing the intensity of pain reported by the participants, aiming to monitor the progression of GSM symptoms during treatment. This assessment will be conducted for each of the symptoms, such as dyspareunia, dryness, irritation/burning, itching, and cytorrhagia, both before and after treatment [35].

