## Discussion

The main objective of this study is to assess the effects of photobiomodulation in women exhibiting symptoms of genitourinary syndrome and urinary incontinence in the postmenopausal phase. Our hypothesis is that this protocol may ameliorate urinary incontinence and alleviate symptoms of postmenopausal genitourinary syndrome, offering a non-hormonal approach to treat this condition. This could potentially serve as a viable option for managing Genitourinary Syndrome of Menopause, contributing to the improvement of signs, symptoms, and quality of life during this phase of women’s lives. Furthermore, this approach may be considered for integration into the public healthcare system, as there are currently no available treatments for genitourinary syndrome in the public healthcare network.

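### The article names no primary outcome, ties its sample size to none, and tests every outcome at 0.05, so the stated type I error does not cover the trial's conclusion

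*Protocol article*

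**What the plan says.** The Statistical analysis section prescribes a t-test or a Wilcoxon-Mann-Whitney test, depending on normality, and then fixes the level for all of them: "All tests will be two-tailed, and the adopted significance level is α = 0.05". It does not rank the outcomes.

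The Outcomes section describes the measures one after another. They are FSFI, ICIQ-SF, VHI, vaginal pH by strip, a VAS, vulvar temperature, vaginal pressure (resting, maximum and minimum) and the 1-hour pad test. On the VAS it says: "This assessment will be conducted for each of the symptoms, such as dyspareunia, dryness, irritation/burning, itching, and cytorrhagia". The abstract lists the same seven instruments (counting pH as part of VHI), also unranked. The words primary and secondary are not applied to any outcome anywhere in the article.

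The section Sample size and participants says: "Considering a type I error of 0.05 and a test power of 80%, the calculated sample size was 60 participants". The effect is a generic standardised one: "for medium (0.750) and large effects (1.000–1.250), a minimum of 30 patients per group is sufficient". The section does not say which outcome that effect or that power refers to.

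The Discussion states a hypothesis in two parts: "this protocol may ameliorate urinary incontinence and alleviate symptoms of postmenopausal genitourinary syndrome". It assigns no outcome to either part.

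**The concern.** A type I error of 0.05 means something for a trial only when it is clear which test, or which set of tests, decides the question. Here the article gives a power and an error rate for an unnamed outcome and then allows every outcome the full 0.05. With many tests on an equal footing, the error rate of the overall conclusion is no longer the 0.05 used in the sample size, and the claim of 80% power has no outcome to refer to.

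The Discussion looks ahead to possible use in the public health system. A claim of that reach should not depend on an outcome picked after the results are known, and a choice made after unblinding cannot credibly repair this.

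**Working it through.** **Inputs from the article.** Two-sided 0.05 for every test (Statistical analysis). Thirty per group, type I error 0.05, power 80%, standardised effect d = 0.75 (Sample size and participants). Equal allocation in blocks of four (Randomization).

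**Inputs that are ours.** The count of tests and the correlations between them. The article gives neither.

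**1. The plan's own figure.** For two means, n per group = 2(1.960 + 0.842)² / 0.75² = 27.9, so 28. With 30 per group the noncentrality is 0.75 × √(30/2) = 2.905. Power is 0.815 by the noncentral t distribution and 0.828 by the normal approximation. The article's statement that 30 per group gives more than 0.80 is correct, for one test at 0.05.

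**2. Count of measures.**

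| Measure | Tests |
|---|---|
| FSFI total | 1 |
| ICIQ-SF | 1 |
| VHI | 1 |
| Vaginal pH | 1 |
| VAS, five named symptoms | 5 |
| Vulvar temperature | 1 |
| Vaginal pressure: resting, maximum, minimum | 3 |
| Pad weight | 1 |
| **Total** | **14** |

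The count is 13 if pH is used only inside VHI, and seven if each instrument gives one test. It would be larger if the six FSFI domains were tested separately or temperature were tested at each session.

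**3. Chance of at least one false positive.** If no outcome is affected and the k tests are independent, this is 1 − 0.95^k:

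- k = 7: 1 − 0.95^7 = 0.302
- k = 13: 1 − 0.95^13 = 0.487
- k = 14: 1 − 0.95^14 = 0.512

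With equally correlated normal test statistics (simulation, 400,000 draws, correlations assumed):

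| Correlation | 7 tests | 14 tests |
|---|---|---|
| 0 | 0.30 | 0.51 |
| 0.3 | 0.27 | 0.44 |
| 0.5 | 0.23 | 0.35 |
| 0.7 | 0.18 | 0.25 |

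Even the smallest entry, 0.18, is more than three times 0.05.

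**4. Power under the remedies** (d = 0.75, 30 per group, noncentral t):

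- One primary outcome at 0.05: 0.815.
- Two primary outcomes under Holm, first step at 0.05/2 = 0.025, planned t-test: 0.726.
- The same step with baseline-adjusted ANCOVA, where the effect becomes 0.75/√(1 − r²). For an assumed baseline correlation r = 0.3 this is 0.786, power 0.77. For r = 0.5 it is 0.866, power 0.85.

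**The case against.** Four objections deserve an answer.

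*A correction for multiplicity belongs in a statistical analysis plan, and none is shown.* This stands. That the article states no correction is not held against it. What remains is that the choice of primary outcome, and the outcome to which the power refers, belong in the protocol. The article also does not leave the level open, since it fixes 0.05 for all tests.

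*A primary outcome may be registered.* The article cites a registration that is not at hand. So the point is only that the article names none. If one is registered, carrying it into the text settles the matter.

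*The error rate is overstated.* A reader might infer that a false positive is about a coin toss. The documents do not support that as the headline. The figure of 51% needs 14 independent tests with no effect on any outcome. Yet pH is one of the five VHI parameters, the three pressures come from one probe, and the VAS items concern related symptoms. The count is also a tally, because the Statistical analysis section does not list which measures will be tested. The range must be given.

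*No rule says that one significant result means success.* Correct. A reader might infer that the trial may declare benefit on whichever outcome crosses 0.05. The article states no success rule at all, and its hypothesis joins incontinence and GSM symptoms with an "and". The fair statement is that nothing in the text prevents such a choice.

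**Conclusion.** The concern holds in a limited form. The article names no primary outcome, attaches its 80% power and 0.05 error to no outcome, and applies two-sided 0.05 to every test. Followed as written, the 0.05 in the sample-size section is not supported for the two-part claim in the Discussion.

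The chance of at least one false positive is roughly 25% to 51% for 14 tests and 18% to 30% for seven instruments. These ranges rest on an inert treatment for all outcomes, on our count, and on assumed equal correlations from 0.7 down to 0.

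The arithmetic behind 30 per group is sound for a single test. What is missing is the outcome it belongs to. A reader might also infer that blinding singles out VHI as the natural primary, because the Blinding section mentions its evaluator. That section also keeps participants unaware of their group, and they are the raters of FSFI, ICIQ-SF and the VAS, so blinding does not decide the choice.

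**What to change.** Before unblinding:

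1. Name one primary outcome and one time point. Use the registered primary if there is one. Otherwise the choice is the sponsor's. The time point must be explicit, because the abstract places the final assessment after the last of four weekly sessions while Study limitations speaks of a 90-day evaluation period.
2. In Sample size and participants, attach the effect of 0.75 and the 80% power to that outcome.
3. In Statistical analysis, limit the confirmatory two-sided 0.05 to that outcome. Report all others as secondary, with estimates and 95% confidence intervals and no confirmatory claim.

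This needs no more patients and keeps power at about 0.81 at d = 0.75 with 30 per group. The cost is that no outcome other than the primary can support a confirmatory claim.

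If the sponsor wants one primary outcome for GSM and one for incontinence, the pair should be controlled at an overall 0.05, for example by Holm, and the power restated. It is then about 0.73 at the first step with the planned t-test, below the stated 80%. Baseline-adjusted ANCOVA would give about 0.77 to 0.85 for an assumed correlation of 0.3 to 0.5, but that changes the planned method and is more than a change of wording.
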